## Design and methods

### Design

This project is primarily designed as comparative effectiveness trial with all intervention sites receiving education concerning a system wide decision to stop recommending aspirin for primary prevention of cardiovascular disease. Six University of Colorado primary care practices in the Denver metro area were block randomized by baseline number of patients on aspirin for primary prevention into one of three intervention arms:

1. Academic detailing and cessation of the primary prevention reminder within the point-of-care clinical decision support system only;

2. Academic detailing with a message asking clinicians to consider stopping aspirin therapy for primary prevention embedded in the point-of-care clinical decision support system; or

3. Academic detailing with the point-of-care message for clinicians as described in arm two above, and a short patient activation form to be given to patients prior to a visit, which asks them to check with their provider concerning their use of aspirin for primary prevention.

The academic detailing consisted of a presentation to the clinicians and staff of each office by the study principal investigator and co-investigator (for larger practices more than one presentation was made), as well as the development and distribution to all primary care clinicians of a one-page information sheet concerning the lack of evidence for low-dose aspirin for primary prevention of cardiovascular disease (CVD). The patient activation form, shown in Additional File 1, was requested by one of the primary care practices prior to this study. All messages on the form, including the aspirin message, were reviewed by clinicians from all primary care practices. Practices were free to request that the forms be turned off at any time during the study, but none did so.

One primary care practice in the system elected to not receive the academic detailing or to participate in the project. This practice will be utilized as a non-randomized temporal control for the intervention practices. An interim analysis will be conducted at six months and the final analysis will be conducted at 15 to 18 months.

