All practices involved in the study were divided into three groups to match the number of patients at baseline on aspirin for primary prevention as closely as possible. After the academic detailing was completed at all sites, practice names were placed on identical cards and blindly drawn from a box by a study team member to allocate them to the patient activation, clinician-only reminder, and academic detailing alone groups. The consort diagram of number of patients randomized to each intervention is shown in Figure 1.

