The primary analysis will include only patients identified as being on aspirin prior to 1 April 2009, when the decision support aspirin message was changed. Aspirin therapy status will be evaluated at six and twelve months after the intervention is initiated at each site. The outcome variable for the analysis will be presence/absence of aspirin therapy at final observation time. We will use a logistic regression approach to determine whether likelihood of aspirin cessation differs among treatment groups, adjusting for clinic (fixed effect), and patient clinical and sociodemographic covariates (age, gender). Time from baseline to last observation will be included as a covariate in the primary analysis. Patients who do not have a follow-up visit during this period will initially be excluded from the analysis, but a sensitivity analysis will be performed, assuming patients with no follow-up visit are still on aspirin therapy. Clinic will initially be included as a fixed effect in analyses because the total number of clinics is too few to achieve stable estimates of covariance components for multilevel modeling. However, additional analyses will be carried out using multilevel modeling with patients nested within physicians because there are an adequate number to include physician as a random effect. Additionally, we will explore using a Cox proportional hazards model with time to cessation as the outcome.

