## Discussion

One of the six practices withdrew from the study prior to the randomization and implementation of the interventions, reducing the patient size (N = 6,016). For this practice, the primary prevention reminder was stopped within the point-of-care clinical decision support system. This practice was treated as a non-randomized temporal control for the intervention practices. Even without randomizing this practice, the power of the study will remain sufficient.

Much research has been done regarding physician behavior change and implementation of new techniques, treatment, and therapies. However, there is not a great deal of literature surrounding effective methods for discontinuation of current practices. Effecting a change in aspirin usage in one or more groups will result in a better understanding of the approaches and efforts needed to stop the use of a previously recommended therapy. If a change in aspirin usage is not detected, a follow-up qualitative analysis at the provider level may provide a better understanding of why providers and patients were unwilling to stop a potentially harmful treatment.

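### The primary logistic model fits arm and clinic fixed effects together although each clinic is in only one arm, so the arm effect is not identified as written

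*Protocol article*

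**What the plan says.** The unit of allocation is the practice. Under Design, the Protocol article says that "Six University of Colorado primary care practices in the Denver metro area were block randomized", each "into one of three intervention arms", and that "practice names were placed on identical cards and blindly drawn from a box by a study team member to allocate them". No practice is described as contributing to more than one arm or as crossing over.

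Under Data analysis approach the primary model is given as "We will use a logistic regression approach to determine whether likelihood of aspirin cessation differs among treatment groups, adjusting for clinic (fixed effect", with age, gender and time to last observation as further covariates. The clinic term is deliberate, because the section returns to it with a reason: "Clinic will initially be included as a fixed effect in analyses because the total number of clinics is too few to achieve stable estimates" of variance components. The outcome is one value per patient: "The outcome variable for the analysis will be presence/absence of aspirin therapy at final observation time". The primary cohort consists of patients who were all on aspirin before the decision-support message was changed.

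The number of randomized practices is given in two ways. Design counts six as randomized. The Discussion says "One of the six practices withdrew from the study prior to the randomization and implementation of the interventions", which leaves five.

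**The concern.** When clusters are allocated, a clinic fixed effect absorbs every difference between clinics, and the arm difference is one of these. Nothing is left within a clinic from which to learn about arm. Few clinics is a fair reason to avoid a clinic random effect, but it does not make a clinic fixed effect compatible with estimating arm.

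This is the primary analysis of the first null hypothesis. An analyst who runs it must depart from the stated model to obtain any arm estimate. That choice would be made with the data in hand, and it can change the direction of the result.

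**Working it through.** **1. The plan's own figure.** The article gives no figure for the model, only 800 patients per arm for 80% power at a 7-point difference. With a two-sided 5% test and base rates near 50% (both assumed), 46.5% against 53.5% gives exactly 800 per arm. The figure therefore reproduces as an individually randomized calculation. It has no bearing on identification, because no number of patients changes the rank of the model.

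**2. Rank of the model.** Inputs: every clinic in one arm (Design); arm and clinic both fixed, plus age, gender and time (Data analysis approach). The split of clinics over arms is assumed, because the flow diagram is not shown.

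Take five clinics split 2/2/1, with clinic 1 of arm 1 as reference. Then arm 2 = clinic 3 + clinic 4, and arm 3 = clinic 5, exactly.

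| Model | Five clinics (2/2/1) | Six clinics (2/2/2) |
|---|---|---|
| Intercept + 2 arm + clinic | 7 columns, rank 5 | 8 columns, rank 6 |
| Same + age, gender, time | 10 columns, rank 8 | 11 columns, rank 9 |
| Clinic + age, gender, time, no arm | 8 columns, rank 8 | 9 columns, rank 9 |
| Arm + age, gender, time, no clinic | 6 columns, rank 6 | 6 columns, rank 6 |

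Adding arm to the clinic-only model raises the rank by 0. The deficit of 2 is the whole 2-df arm effect. Splits of 1/2/2 and 3/1/1 give the same result.

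**3. What a dropped-term fit would report.** Assumed cessation: 15% and 25% in the two arm 1 clinics, 20% in both arm 2 clinics. If one clinic term per arm is dropped, the arm 2 coefficient compares the two reference clinics.

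- Reference clinic at 15%: (0.20/0.80) / (0.15/0.85) = 0.250/0.176 = 1.42.
- Reference clinic at 25%: (0.20/0.80) / (0.25/0.75) = 0.250/0.333 = 0.75.
- Nested sum-to-zero coding (mean logits): exp[−1.386 − (−1.735 − 1.099)/2] = exp(0.030) = 1.03, whichever clinic is the reference.

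**4. A separate consequence: clustering.** Any single-clinic contrast carries binomial error only. With m patients per clinic, naive variance = 2p(1−p)/m and true variance = 2[ICC·p(1−p) + (1−ICC)·p(1−p)/m]. Their ratio is D = 1 + (m−1)·ICC, and the rejection rate under no effect is 2[1 − Φ(1.96/√D)].

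Assumed m: 4,400 patients without CVD on aspirin, scaled by 6,016/6,827 and divided by five clinics, gives about 775.

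| Assumed ICC | D | Rejection under no effect |
|---|---|---|
| 0.001 | 1.77 | 14% |
| 0.01 | 8.74 | 51% |
| 0.05 | 39.7 | 76% |

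**5. Deleting the clinic term alone is not enough.** The patient-level model then estimates arm but ignores clustering. With 800 per arm in two clinics of 400 (assumed), the design effect 1 + 399·ICC is 3.0, 5.0 and 9.0 at ICCs of 0.005, 0.01 and 0.02. Power for 46.5% against 53.5%, once clustering is allowed for, is about 37%, 24% and 15%, before any further loss from few degrees of freedom.

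**The case against.** The strongest reply is that clinic may be coded as nested within arm, and that a journal article may leave such coding to an analysis plan not shown here. That coding does give an estimate, and one that does not depend on the reference clinic. So a reader who infers that the arm effect cannot be estimated at all goes too far: it is not identified without a constraint, and the article states none. What survives is that the nested contrast describes only these particular clinics. It has no between-clinic variation in its standard error, so it cannot separate the intervention from differences the clinics would have shown anyway.

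Software behavior also varies. A program may stop, print a note, or drop arm terms instead of clinic terms. The flip between 1.42 and 0.75 is one possible outcome among several.

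A reader might also take 51% as the false-positive rate of the planned analysis, or as the cost of the rank deficiency. It is neither. It is the cost of ignoring between-clinic variance in a one-clinic contrast, at one assumed ICC. The 775 assumes that the withdrawn practice had the same share of eligible patients as the others, and it is taken before patients without follow-up are excluded.

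The other planned analyses do not rescue the primary one. The physician random-effect model is additional, is not said to omit clinic, and leaves out the randomized level if it does. The Cox model is exploratory. Repeated measures are mentioned only for the diabetes hypothesis.

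**Conclusion.** The concern holds as a defect of the stated primary model. With arm and clinic both fixed and one final outcome per patient, the arm effect is short by its full 2 degrees of freedom, under five or six clinics alike. This rests only on the allocation of whole practices and on the model as written, not on any assumed rate.

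The odds ratios and rejection rates are illustrations. They depend on assumed cessation rates, ICCs, clinic sizes and clinic split, and the rejection rates belong to the clustering problem rather than to the aliasing. The documents do not support the stronger statements that no coding could yield an estimate or that any particular type I error rate applies to this trial.

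**What to change.** Remove the clinic fixed effect from the primary model. Compare covariate-adjusted clinic-level cessation proportions between arms, using between-clinic variation for inference, with degrees of freedom equal to the number of randomized clinics minus 3. That is 5 − 3 = 2 or 6 − 3 = 3, so Design and Discussion must first be reconciled on how many practices were randomized.

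State plainly that intervals will be much wider: on 2 df the two-sided 5% critical t is 4.30, against 1.96 for the normal. This is a real loss of precision, and it reflects how few units were randomized. The change costs a rewording of the analysis section and needs no new data.

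As an optional supporting analysis, a model with clinic, period and arm-by-period is identified (five clinics, ten clinic-period cells: 8 columns, rank 8). It needs a pre-intervention cohort with cessation follow-up over a comparable period. The article says pre-intervention data were collected from the same system but does not describe such a cohort, so this depends on whether one can be extracted from the EHR. It should not replace the primary analysis by default.

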### Human subjects protection

This study was approved by the Colorado Multiple Institution Review Board. It was also registered on ClinicalTrials.gov, identifier: NCT01247454. The study was granted a waiver of consent at the patient level.

## Discussion

One of the six practices withdrew from the study prior to the randomization and implementation of the interventions, reducing the patient size (N = 6,016). For this practice, the primary prevention reminder was stopped within the point-of-care clinical decision support system. This practice was treated as a non-randomized temporal control for the intervention practices. Even without randomizing this practice, the power of the study will remain sufficient.

Much research has been done regarding physician behavior change and implementation of new techniques, treatment, and therapies. However, there is not a great deal of literature surrounding effective methods for discontinuation of current practices. Effecting a change in aspirin usage in one or more groups will result in a better understanding of the approaches and efforts needed to stop the use of a previously recommended therapy. If a change in aspirin usage is not detected, a follow-up qualitative analysis at the provider level may provide a better understanding of why providers and patients were unwilling to stop a potentially harmful treatment.
